**Methods:**

A comparative, parallel-group, randomized double-blind trial assessing the efficacy, safety, and tolerability of acute (4 weeks) and maintenance (24 weeks) use of IM ketamine (0.75 mg/kg) vs. active control (escitalopram 15 mg and aripiprazole 5 mg) in individuals with moderate-severe intensity TRD (no psychotic symptoms) with or without suicide risk will be conducted. Patients with TRD (18–40 years) will be randomized and blinded to receive ketamine IM or active treatment at a 1:1 ratio for 4 weeks (active treatment) and 24 weeks (maintenance treatment). Subjects will be assessed using clinical scales, monitored for vital signs (VS) after application of injectable medication, and undergo neuropsychological tests. The primary outcome will be changed on the Montgomery-Åsberg Depression Rating Scale (MADRS) during the course of the trial. The study is in running.

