## Methods

### Design and study populations

A comparative, parallel-group, randomized, double-blind trial is to be conducted involving an anti-depressant intervention. The experimental group (EG) will use the experimental substance [ketamine IM 0.75 mg/kg, oral placebo (morning), and oral placebo (evening)], while the control group (CG) will use an active treatment administered orally [escitalopram 15 mg (morning), aripiprazole 5 mg (evening) and placebo IM]. The study will be carried out by the Institute of Psychiatry of the University of São Paulo Medical School (HCFMUSP), in conjunction with the Center for Mind Health Studies (NUPE) in the Vale do Itajaí, Santa Catarina state, Brazil. The study is called the KETAMIM project and is Registered Under No. NCT04234776 on the www.ClinicalTrials.gov platform. The study phases and methodological aspects comply with the recommendations of the CONSORT (Consolidated Standard of Reporting Trials) statement and with Good Clinical Practice guidelines (GCP) (65, 66). The study is in running.

The study shall entail 5 phases: (1) Dissemination (P0): patients referred by health professionals, dissemination in the press or online media; (2) Pre-treatment (PI): ~2 weeks for the baseline assessment of candidates for study entry; (3) Therapeutic trial (PII): 4 weeks for ketamine use 3 times weekly and of daily oral medications, as well as placebos for both groups, characterizing acute treatment of the disease; (4) Maintenance (PIII): 24 weeks for weekly ketamine use and maintenance of standard treatment and respective placebos; (5) Post-treatment (PIV): 4 weeks for assessing patients after use of ketamine, maintenance oral medication or placebo.

A total of 88 patients with TRD (≥2 failed trials using anti-depressants, plus ECT as an alternative or otherwise) of moderate-severe intensity [according to criteria of Diagnostic and Statistical Manual of Mental Disorders (DSM-5)], and the diagnosis confirmed by the Portuguese version of the clinical interview of the DSM-IV, will be recruited (67). Patients will be block randomized using a computer-generated list into one of the two interventions (1:1 ratio), EG or CG (68). A nurse blinded to the allocation will administer ketamine or saline IM, placebo orally, or the active treatment, respectively.

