### Inclusion and exclusion criteria

**The following individuals will be eligible for study inclusion:** Subjects residing in Itajaí valley (Santa Catarina state, Brazil); adults (age 18–40 years) with a primary diagnosis of TRD based on clinical evaluation and confirmed by the SCID-IV [research version (TRD defined as failure of 2–5 clinical trials with anti-depressants including ECT)]; moderate-severe intensity disease [clinical criteria and/or score ≥14 on the Hamilton Depression Rating Scale (17-item HAM-D)]; with no psychotic symptoms; not presenting an imminent risk of suicide (as indicated by clinical evaluation and HAM-D) and/or murder; with anxiety disorders (secondary); with compensated clinical comorbidities and; literate and able to understand the tasks requested (69). Patients and/or legal guardians must be aware of the nature of the study and give consent by signing the Free and Informed Consent form. All patients will undergo a physical and neurological examination, laboratory tests, and an electrocardiogram (ECG) to ascertain their comorbid clinical and/or uncompensated conditions. **The following individuals will be excluded from the study:** Subjects exhibiting imminent risk of suicide, presenting bipolar spectrum disorders or other diagnosed psychiatric conditions (primary); psychoactive substance dependence within the last year; intellectual deficit; allergy to ketamine; and glaucoma. Fertile women must be in use of a clinically acceptable method of birth control [oral contraceptive and/or condom (only unfollowed topic in GCP)]. In the event of clinical doubt regarding pregnancy, a test for beta-human chorionic gonadotropin (βHCG) hormone will be ordered. Patients who become pregnant during the study period will be excluded and referred for obstetric care. The medication wash-out period required before visit 0 will be 1 week for antipsychotics, antidepressants [except fluoxetine (4 weeks)], and for mood stabilizers. No other medications with psychiatric action will be allowed during the study, except for Lorazepam and Zolpidem for patients in the use of a benzodiazepine or hypnotic agent.

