### Measures and outcome variables

The study will assess (given in Table 1):

Sociodemographic variables: gender, marital status, ethnicity, number of children, income, education, and employment.Clinical characteristics over the life course: clinical and psychiatric comorbidities, smoking, family history of mood disorders, prior pharmacological treatment and ECT, number of mood episodes, previous psychiatric admissions, suicide attempts, currently receiving psychotherapy, and history of sexual, or physical abuse.Clinical history: visits to the emergency room, attempted suicides, or psychiatric hospitalizations.The Montgomery-Åsberg Depression Rating Scale (MADRS) (70, 71): will be applied as a primary outcome measure 3× per week for the first month (PII), 1× per week for 6 months (PIII), and 1× per week (PIV) for 1 month.The Hamilton Rating Scale for Depression (HAM-D) (72, 73): will be applied once in PI to assess symptom severity and again 3× per week for 1 month (PII), 1× per week for 6 months (PIII), and 1× per week (PIV) for 1 month.Vital signs (VS): pulse oximetry, heart monitoring, breathing rate, heart rate, and blood pressure will be checked continuously using non-invasive methods. VS to be monitored 3× per week for the 1st month (PII) and 1× week (PIII) for 2 h continuously after completion of each application.Global Clinical Impression (GCI) scale: this will be applied 3× a week for 1 month (PII), 1× week for 6 months (PIII), and 1× week (PIV) to assess disease severity, global improvement of the condition and hence, treatment efficacy (74).Depression Thoughts Scale (DTS): the DTS will be applied at visit one (V-1), V11, and V-39 to assess for thought distortions (75, 76).Clinician-Administered Dissociative States Scale (CADSS): this will provide a measure of the dissociative effects of ketamine and will be applied 3× per week for the 1st month (PII), and 1× per week for 6 months (PIII), ~1 h after application of injections (77).Young's Mania Rating Scale (YMRS): this scale will be employed in this study to assess manic switching as an adverse effect of the medications and applied 3× week for the 1st month (PII) and 1× week for 6 months (PIII), ~1 h after application of injections (78).Brief Psychiatric Rating Scale (BPRS): Sub-item 12 of the scale will be used for detecting the presence of psychotic symptoms arising after application of ketamine, applied 3× week for 1 month (PII) and 1× week (PIII), ~1 h after application of injections (79).Udvalg Kliniske Undersoegelser Side Effect Rating Scale (UKU-SERS): this will be used to determine the presence of side effects of the medications used and will be applied 3× week for the 1st month (PII) and 1× week (PIII) thereafter, around 1 h after application of injections (79).World Health Organization Quality of Life, brief version (WHOQOL-Bref): this scale will be applied at V-1, V-11, and V-35 (80).Sheehan Disability Scale (SDS): this scale will be applied at V-1, V-11, and V-35 (81).

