### Sample size calculation

The sample size was calculated based on a similarly designed RCT (45). Assuming a statistical power of 90% with a clinically significant minimum effect of 0.5 (Cohen's d) and alpha 5%, a total of 88 subjects will be needed (44 in the EG and 44 in the CG). Given this is a long-duration study, a drop-out rate of 10–20% was estimated.

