### Statistical analysis

All analyzes will be performed using the Statistical Package for the Social Sciences-SPSS® (82). Specific and sociodemographic variables will be expressed generally and between intervention groups in relative and absolute frequencies, means, medians, standard deviation, and 95% confidence interval. Continuous variables will be evaluated by the *T*-student or U-Mann Whitney-test according to their distribution and the qualitative ones by the *X*^2^-test. The distribution of variables will be evaluated using the Shapiro Wilk. The global significance level adopted is 0.05. To determine the effects of intervention throughout the study (main outcome and other scales), repeated measures ANOVA (two-way) will be applied, considering the temporal effect of visits (v-0 to v-final) and the intervention effect (EG × CG). In identifying the significant interaction effect, one-way repeated measures ANOVA test or its non-parametric alternative (Friedmann test) will be performed to verify that the effect is independent of treatment. Contingency tables and *X*^2^-tests will be applied to compare responders and non-responders in the intervention groups. Analysis using intent-to-treat (ITT) will be employed to assess the results (83). Vital signs will be assessed using two repeated measures ANOVA (two-way). First, considering the effect of the intervention immediately (3 evaluations at each visit) and the second, evaluating the effect of the intervention on VS over time (acute and maintenance treatment).

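### The MADRS analysis uses visit and arm only, so a pre-treatment severity score the trial already collects is not used for adjustment: the test stays valid but loses power

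*Protocol article*

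**What the plan says.** **Outcome.** The abstract (Methods) states: "The primary outcome will be changed on the Montgomery-Åsberg Depression Rating Scale (MADRS) during the course of the trial".

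**Model.** Statistical analysis sets out one model, whose purpose is given as "To determine the effects of intervention throughout the study (main outcome and other scales"). It reads: "repeated measures ANOVA (two-way) will be applied, considering the temporal effect of visits (v-0 to v-final) and the intervention effect (EG × CG"). The two factors are visit and arm. No covariate is named there, and the article mentions baseline adjustment nowhere else.

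**Pre-treatment severity.** Measures and outcome variables says of the HAM-D that it "will be applied once in PI to assess symptom severity", and Table 1 ticks HAM-D under Baseline. PI is described in Design and study populations as "Pre-treatment (PI): ~2 weeks for the baseline assessment of candidates for study entry".

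**Visit 0.** It is never defined. The nearest statement is in Inclusion and exclusion criteria: "The medication wash-out period required before visit 0 will be 1 week" for most drugs. That suggests a pre-treatment visit. The MADRS, however, "will be applied as a primary outcome measure 3× per week for the first month (PII"), so the text lists it only from the treatment phase onward, and Table 1 has no Baseline tick for it.

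**The concern.** A severity score taken before treatment usually predicts later severity. Entered as a covariate, it removes part of the between-patient variation from the comparison of arms. The planned model does not use it in this way. Its arm effect leaves between-patient severity in the error term. If v-0 is a pre-dose visit, the arm-by-visit interaction uses it only through changes from v-0, which is never more efficient than adjusting for it and lets a chance baseline difference act through regression to the mean.

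What is at stake is precision. With 88 patients the interval for the difference between arms is already wide. The principal hypothesis is that ketamine has similar efficacy to the active control, and a claim of similarity depends on how narrow that interval is.

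**Working it through.** **Inputs from the article:** 44 per arm, d = 0.5, alpha 5% and 90% power (Sample size calculation). Two-sided testing is my assumption, as sidedness is not stated. Visits after baseline: 12 acute + 24 weekly + 4 post-treatment = 40 (Intervention; Measures and outcome variables).

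**Inputs assumed, because the article gives none:** ρ, the correlation of baseline with a later score, 0.3 to 0.7; and for averaged visits r, the correlation between two post-baseline scores, 0.6 to 0.7. Each score has SD 1, and the arm effect is the same at every post-baseline visit.

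**The plan's own figure.** n per arm = 2(1.960 + 1.282)²/0.5² = 84.1, so 85 per arm for 90% power. The stated 44 per arm does not reproduce. With 44 the noncentrality is 0.5·√(44/2) = 2.345, and the t-test on 86 df has power 64.0%. That mismatch is a separate issue; 64% is the starting point here.

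**Single visit.** Residual SD: final score 1; change from v-0 √(2(1−ρ)); baseline-adjusted √(1−ρ²), with one further df lost.

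| ρ | Final score | Change from v-0 | Adjusted |
|---|---|---|---|
| 0.3 | 64.0% | 50.0% | 68.1% |
| 0.4 | 64.0% | 56.2% | 71.6% |
| 0.5 | 64.0% | 64.0% | 76.3% |
| 0.6 | 64.0% | 73.7% | 82.6% |
| 0.7 | 64.0% | 84.9% | 90.1% |

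Adjustment cannot lose to the change score, apart from the one df, because 1−ρ² = (1−ρ)(1+ρ) ≤ 2(1−ρ). Against the unadjusted final score, the interval narrows by 1−√(1−ρ²): 5%, 13% and 29% at ρ = 0.3, 0.5 and 0.7.

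**Arm effect averaged over visits, K = 40.**

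- Post-baseline mean: variance V = (1 + 39r)/40, effect 0.5.
- Mean including v-0, as planned: variance (1 + 40²V + 80ρ)/41², effect 0.5 × 40/41 = 0.488.
- Post-baseline mean adjusted for baseline: variance V − ρ², effect 0.5.

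| ρ | r | Planned (with v-0) | v-0 dropped, no covariate | Adjusted | Total gain, points |
|---|---|---|---|---|---|
| 0.3 | 0.6 | 83.4% | 84.4% | 89.5% | 6 |
| 0.3 | 0.7 | 77.9% | 78.7% | 83.9% | 6 |
| 0.5 | 0.6 | 82.9% | 84.4% | 97.2% | 14 |
| 0.5 | 0.7 | 77.3% | 78.7% | 92.9% | 16 |

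For ρ = 0.5, r = 0.7: V = 28.3/40 = 0.7075. The planned variance is (1 + 1132 + 40)/1681 = 0.698, and the adjusted variance is 0.7075 − 0.25 = 0.4575.

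Dropping v-0 alone adds about 1 to 1.5 points. The rest comes from the covariate.

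**Arm-by-visit interaction.** With one common correlation of 0.3, 0.5 or 0.7 among all visits and a constant effect after v-0, the noncentral F test has power 36%, 51% and 78% with 12 post-baseline visits, and 21%, 30% and 54% with 40. The contrast with v-0 is spread over one df per visit.

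**The case against.** **The test is not wrong.** Under randomisation, the two-way repeated measures ANOVA does not bias the arm comparison for want of a covariate. A reader might infer that chance baseline imbalance makes the result biased or inflates the type I error. The article does not support that: imbalance matters only conditionally, in a given sample. This objection stands, and it limits the point to efficiency.

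**v-0 may hold no MADRS.** A pre-dose MADRS is implied by the model's visit range but not confirmed by the schedule. If none is taken, the remarks on change from v-0 and on averaging it in do not apply, and what remains is adjustment for HAM-D, a different scale rated in a pre-treatment phase of about two weeks. Its correlation with later MADRS is unknown, and the severity threshold for entry may lower it. This also stands. It is why the fix depends on the schedule and why the range starts at 0.3, where the gain over the final score is only 4 points.

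**Averaging in v-0 looks like a serious dilution.** A reader might infer this because no treatment effect can exist at that visit. Over 40 visits it costs about 1 to 1.5 points, so it is not a main argument.

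**The single-visit figures are not the planned test.** That is fair. The averaged-visit and interaction figures address the stated model, and the direction is the same. All the power figures assume complete data on 44 per arm, while the article expects 10–20% drop-out. At ρ = 0.5, with 39.6 or 35.2 per arm, single-visit power is 59% or 54% unadjusted and 72% or 67% adjusted.

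**Covariates are often left to the full plan.** This is commonly so, but here the article writes the model out with its factors, and the model as written has no covariate.

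**Conclusion.** The point holds as a matter of efficiency. The stated model leaves an already collected pre-treatment severity value unused as a covariate. At one visit, adjusted power is 68% to 90%, against 64% for the final score and 50% to 85% for change from v-0. For the effect averaged over about 40 visits, power rises from 77–83% to 84–97%, a gain of about 6 to 16 points.

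The direction does not depend on the assumed values once the baseline correlation is more than trivial; the size does, and the article gives none of the correlations. The figures also assume two-sided testing, a constant effect and complete data.

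A reader might infer that adjustment rescues the claim of 90% power with 88 patients. For a single visit that would need a correlation of about 0.69, which nothing in the article supports. The sample size needs its own correction.

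**What to change.** In Statistical analysis, replace the two-factor model for the main outcome by a repeated-measures model of post-baseline MADRS on arm, visit, arm-by-visit and one pre-specified baseline covariate that is the same for every patient. Use the pre-dose v-0 MADRS if the schedule confirms it is collected, and otherwise the HAM-D from PI. Do not switch scale from patient to patient, since that would mix two scales in one covariate.

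Define v-0, and reconcile the MADRS schedule in Measures and outcome variables and in Table 1 with the v-0 in the model. Apply the same approach to the other scales that have a pre-treatment value. The trial is described as running, so the change should be fixed before unblinding.

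**Cost.** A change of wording, one degree of freedom for a common baseline slope, and no new patients or measurements. SPSS, the package named in the article, can fit the model. A baseline-by-visit term is optional and would cost about one coefficient per visit, roughly 40 here.

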### Intervention

Two groups will be formed: a study group and an active control group. The study group will receive dextroketamine chloralhydrate IM (0.75 mg/kg) plus 2 placebo tablets orally, one in the morning and the other at night. The active control group will receive saline solution IM plus one of the alternative therapies for TRD: escitalopram 15 mg (morning) or aripiprazole 5 mg (night) (10). Injections will be applied alternately to gluteal muscles in the external upper quadrants. For 4 weeks (1 month), applications will be applied on Mondays, Wednesdays, and Fridays (giving a total of 12 interventions). For the ensuing 6 months, applications will be weekly (giving a total of 24 interventions). For 4 weeks (1 month), participants will continue to receive the tablets (active treatment or placebo) and be monitored. Safety parameters: vital signs will be monitored continuously by the researchers for 2 h post-application: fingertip pulse oximetry, heart rate, breathing rate, blood pressure, and electrocardiography. Abnormal blood pressure will be defined as low <90/60 mmHg and high >140/90 mmHg. Abnormal heart rate will be defined as <60 or >100 bpm. Abnormal breathing rate will be defined as <10 cycles/min or >20 cycles/min. Low oxygen saturation will be defined as levels <95%. Collateral symptoms such as nausea and vomiting will be managed using ondansetron 8 mg sublingually (SL). Individuals presenting episodes of anxiety, hallucinations, or intense dissociative effects will be given clonazepam SL 0.25 mg. An emergency team will be deployed in the event of serious acute events such as heart arrhythmia or prolonged hypertension. Patients will be placed under observation in a quiet comfortable environment and will be cleared to leave after 2 h, accompanied by a competent adult.

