### Reasons for withdrawal or termination

Subjects who meet one or more of the criteria outlined below will be withdrawn from the study:

Intolerance to medications;Abnormal results on lab tests;Serious adverse event;The above-mentioned items will be assessed individually by the team according to medical criteria. Prolonged arterial hypertension, serious allergies, abnormal heart rate, or worsening of pre-existing diseases, among others, will be checked. Manic switching, imminent risk of suicide, attempted suicide, severe psychotic symptoms, aggressiveness, etc. will constitute grounds for study withdrawal.Relapse or lack of response in Phases II or III. Lack of response will be defined as reduction or maintenance of scores on the index scale of ≤25%, whereas relapse will be the attainment of scores <50% in individuals who had achieved remission or response during the study.Two consecutive visits missed;Withdrawal of consent for the study.

Patients who discontinue the study shall be given guidance to continue outpatient psychiatric treatment.

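### Unless missing values are imputed, the repeated-measures ANOVA over 40 MADRS visits drops every patient with one empty visit, which does not fit the stated ITT analysis

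*Protocol article*

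**What the plan says.** All references are to the protocol article.

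- **Model.** Statistical analysis, for the main outcome and other scales: "repeated measures ANOVA (two-way) will be applied, considering the temporal effect of visits (v-0 to v-final"), crossed with the intervention effect. A one-way repeated-measures ANOVA or a Friedman test follows if the interaction is significant.
- **Software.** "All analyzes will be performed using the Statistical Package for the Social Sciences-SPSS".
- **Population.** "Analysis using intent-to-treat (ITT) will be employed to assess the results". No imputation, mixed model or other treatment of empty visits is named.
- **Schedule.** Measures and outcome variables makes MADRS the "primary outcome measure 3× per week for the first month (PII), 1× per week for 6 months (PIII), and 1× per week (PIV") for one month. Intervention confirms the counts: "applications will be applied on Mondays, Wednesdays, and Fridays (giving a total of 12 interventions") and then "applications will be weekly (giving a total of 24 interventions").
- **Attendance rule.** Reasons for withdrawal or termination lists "Two consecutive visits missed". A single isolated miss does not meet this criterion.
- **Drop-out.** Sample size calculation expects 10–20% and plans 88 patients, 44 per arm.

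**The concern.** Standard repeated-measures ANOVA in SPSS holds one row per patient with one column per visit, and drops the row if any column is empty. The Friedman test also needs complete blocks. With 40 columns, even very good attendance leaves many patients with at least one gap.

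The attendance rule keeps those patients in treatment and follow-up, and the analysis then discards all their data. Patients who withdraw for any reason also have empty later visits and are discarded. The primary comparison would rest on patients with perfect attendance, not on everyone randomised. That costs power. It can also bias the comparison if attendance is related to how ill patients are. The point is not that missing-data text is absent from a condensed article. It is that the model named for this visit schedule, in its standard form, does not fit the population named beside it.

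**Working it through.** **1. Number of visits.** PII: 3 × 4 = 12. PIII: 24. PIV: 4. Total 12 + 24 + 4 = 40. This agrees with the visit numbering, whose highest visit is V-39 (V-0 to V-39 is 40 visits).

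**2. Share of patients with all 40 values.** The per-visit miss rate q is not in the document, so a range is assumed.

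- *Independent misses:* P(complete) = (1 − q)^40.
- *Misses clustered within patients:* beta-binomial with intraclass correlation ICC, s = 1/ICC − 1, α = qs, β = (1 − q)s, and P(complete) = Π (β + k)/(α + β + k) for k = 0 to 39. ICC 0.05 to 0.10 is also an assumption.

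| q | Independent | Complete of 88 | Clustered, ICC 0.05–0.10 |
|---|---|---|---|
| 1% | 67% | 59 | 80–85% |
| 2% | 45% | 39 | 64–73% |
| 3% | 30% | 26 | 52–62% |
| 5% | 13% | 11 | 33–45% |

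These shares are before any other drop-out.

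**3. Patients kept by the attendance rule but lost to the analysis.** With independent misses, a two-state recursion (last visit attended or missed) gives the probability of never missing two visits in a row over 40 visits. Subtracting P(complete) leaves those who stay but have a gap:

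- q = 1%: 99.6% − 66.9% = 33%
- q = 2%: 98.5% − 44.6% = 54%
- q = 3%: 96.6% − 29.6% = 67%
- q = 5%: 91.1% − 12.9% = 78%

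**4. Power of the named test.** For the between-group F test averaged over m = 40 visits, the noncentrality is λ = N f² m / [1 + (m − 1)ρ], with f = d/2 = 0.25, α = 0.05 and F on 1 and N − 2 degrees of freedom. The correlation ρ = 0.5 is assumed.

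- N = 88: λ = 88 × 0.0625 × 40 / 20.5 = 10.73, power 90%. This matches the plan's stated 90% at 88, although the article does not say that this was its calculation.
- N = 59 (q = 1%, independent): λ = 7.20, power 75%.
- N = 39 (q = 2%, independent): λ = 4.76, power 57%.
- Clustered misses: at q = 1%, N is about 71–75 and power 82–85%. At q = 2%, N is about 57–64 and power 73–79%.
- Independent misses plus 10–20% drop-out: at q = 1%, 53–47 complete patients and power 70–65%. At q = 2%, 35–31 complete patients and power 52–47%.

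**5. Multivariate tests.** Forty visits give 39 within-patient contrasts. Two groups leave N − 2 error degrees of freedom, so N − 2 ≥ 39 is needed, that is, at least 41 complete patients. With independent misses at 2%, 39 remain.

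**The case against.** **ITT and this ANOVA are not strictly incompatible.** A reader might infer that the stated method cannot deliver ITT at all. The document does not support that. It nowhere says complete-case, and the same ANOVA on imputed data would keep all 88 patients. A fuller protocol or SAP may hold such a rule. This objection stands, and the point is therefore conditional on no imputation. It does not remove the point, because the article fixes a model that in its standard form deletes patients, while a method without that defect is available in the same software.

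**Isolated misses and withdrawals are one missing-data problem.** This is fair. A rule that fills visits after withdrawal would usually fill isolated gaps too. Both groups are therefore counted here.

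**The size rests on inputs that the document does not give.** This is also fair. Independence is close to a worst case, and clustering reduces the loss considerably, as the table shows.

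**Some stronger statements do not hold:**

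- The 64% power of a two-sample t-test with 44 per arm at d = 0.5 is not the right starting point. It belongs to a single-time-point comparison, not to the ANOVA named, and raises a separate sample-size question.
- Having fewer than 41 complete patients does not stop the analysis. Only the multivariate within-subject tests fail. The between-group and univariate within-subject tests still run, on the selected subset.
- The loss over 40 visits does not extend to every scale. DTS, WHOQOL-Bref and SDS are each listed for three visits in Measures and outcome variables.

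**Conclusion.** The concern holds in conditional form. Unless missing values are imputed, which the article does not state, the named ANOVA and its Friedman follow-up exclude any patient with one empty visit out of 40. That takes in patients who stay in the study with an isolated miss and the 10–20% expected to drop out (about 9 to 18 of 88). The ITT statement is then not met.

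The direction of the loss follows from the method, but its size does not follow from the document. At an assumed 1–2% miss rate, complete records range from 45–67% of patients (independent) to 64–85% (clustered), before drop-out. Power of the between-group test falls from 90% to about 57–75% under independence, given d = 0.5 at every visit and a within-patient correlation of 0.5. With clustering the fall is smaller, to about 73–85%.

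A reader might also infer a treatment effect biased by a known amount. Bias arises only if attendance is related to severity. The document gives nothing from which to size it, so no bias figure should be quoted as established.

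**What to change.** For MADRS and the other scales rated at every visit (not DTS, WHOQOL-Bref or SDS), replace the repeated-measures ANOVA with a linear mixed model fitted by REML in SPSS MIXED:

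- Include all randomised patients and every observed visit, and state that no patient is removed for an incomplete visit record.
- Use fixed effects for arm, visit and arm-by-visit.
- Keep the first MADRS separate as the baseline value. Do not average it with later PII visits: Table 1 marks no MADRS in its Baseline column, so V-0 may hold the only pre-treatment rating, and averaging could also blur the rapid effect under study.
- Pre-specify a covariance structure that is feasible for the number of visits. An unstructured matrix for the 39 later visits has 39 × 40 / 2 = 780 parameters, too many for 88 patients.
- Keep the complete-case ANOVA only as a sensitivity analysis.

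If an imputation rule already exists in a fuller document, state it next to the ITT sentence.

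**Cost.** Analysis wording and syntax only, with no new data or visits. The article says that the trial is running, so the change should be dated before unblinding. The downside is that the result relies on a missing-at-random assumption and on the chosen covariance structure.

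### The primary MADRS analysis runs to the final visit, so as written it includes the month after ketamine has stopped; that month alone can make the group-by-visit interaction significant, and it dilutes the group effect

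*Protocol article*

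**What the plan says.** The Abstract (Methods) defines the outcome without a time point: "The primary outcome will be changed on the Montgomery-Åsberg Depression Rating Scale (MADRS) during the course of the trial". Statistical analysis then gives the model: "To determine the effects of intervention throughout the study (main outcome and other scales), repeated measures ANOVA (two-way) will be applied". The two factors of that model and its visit range are spelled out next: "considering the temporal effect of visits (v-0 to v-final) and the intervention effect (EG × CG"). No phase is excluded, and the last visit is not given a number.

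Measures and outcome variables sets the MADRS schedule. The scale "will be applied as a primary outcome measure 3× per week for the first month (PII), 1× per week for 6 months (PIII"). Weekly rating then goes on into the post-treatment phase: "1× per week for 6 months (PIII), and 1× per week (PIV) for 1 month".

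PIV treatment is described twice:

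- Intervention, after the weekly injections: "participants will continue to receive the tablets (active treatment or placebo) and be monitored". No injection is mentioned for this month.
- Design and study populations, on PIV: "4 weeks for assessing patients after use of ketamine, maintenance oral medication or placebo".

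The significance statement is brief: "The global significance level adopted is 0.05". A significant interaction is to be followed by a one-way repeated-measures ANOVA or Friedman test, which is not said to separate the phases. For vital signs over time, by contrast, the same section names the acute and maintenance phases as the window.

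**The concern.** The trial asks whether IM ketamine works during 4 weeks of acute and 24 weeks of maintenance use. PIV answers a different question: what happens after the injections stop. The Introduction itself says that ketamine's antidepressant effect lasts only days or weeks, so it is foreseeable that the between-arm difference in PIV will not match the one before it.

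Putting both periods into one ANOVA has two consequences. A significant interaction, the term for which the plan specifies a follow-up test, could come entirely from the off-ketamine month and be read as evidence about treatment. And the group effect, averaged over all visits, would mix on-drug with off-drug weeks. The principal hypothesis is similar efficacy, so this second effect is not simply conservative: an on-drug difference that shrinks because it is averaged with a month of no difference looks more like similarity.

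**Working it through.** **Visit count (inferred).** Intervention gives 12 injection visits in PII and 24 in PIII. Weekly rating over 4 weeks of PIV adds 4. So 12 + 24 + 4 = 40, or V-0 to V-39, and PIV is 4/40 = 10% of the ratings. The labels V-11, V-35 and V-39 in Measures fit the ends of PII, PIII and PIV on this count.

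**Inputs.** From Sample size calculation: 44 per arm, alpha 0.05 and an effect of 0.5 SD. The plan gives no power figure for this window, so there is none to reproduce. The documents give no correlation between visits, so it is assumed and varied. Tests are two-sided and data complete.

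**Check 1: interaction, arms identical on drug and 0.5 SD apart in PIV only.** With n per arm, SD 1 and common correlation ρ, the interaction F test has noncentrality λ = (n/2) × Σ(dⱼ − d̄)² / (1 − ρ).

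- d̄ = 0.5 × 4/40 = 0.05.
- Σ(dⱼ − d̄)² = 4 × 0.5² − 40 × 0.05² = 1.0 − 0.1 = 0.9.
- ρ = 0.5: λ = 22 × 0.9/0.5 = 39.6 on 39 and 86 × 39 = 3,354 df. Rejection is 95%.
- ρ = 0.7: λ = 22 × 0.9/0.3 = 66. Rejection is 99.9%.

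Equal correlation flatters this test. Simulations of 1,000 trials with the Greenhouse-Geisser correction and correlation that decays with visit lag gave:

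| Assumed correlation at lag k | V-0 to V-39 | V-0 to V-35 |
|---|---|---|
| 0.4 + 0.6 × 0.8^k | 51% | 4% |
| 0.3 + 0.7 × 0.9^k | 39% | 6% |

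Another set of runs, over three assumed covariances, gave 51–91% with PIV and 4–6% without. With 35 per arm (88 less 20% dropout), the two decaying structures gave 37% and 29%.

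**Check 2: group main effect, same scenario.** The 0.5 SD enters the visit average as 0.05 SD. Rejection is 6% at both ρ = 0.5 and ρ = 0.7, close to nominal. PIV alone does not drive this test.

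**Check 3: group main effect, 0.5 SD on drug and zero in PIV.** The visit average is 0.5 × 36/40 = 0.45 SD. Under equal correlation the variance of a patient's mean is (1 + (m − 1)ρ)/m for m visits, and the noncentrality is the average difference × √22 / SD of that mean.

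- ρ = 0.5, 40 visits: variance 20.5/40 = 0.5125, noncentrality 0.45 × 4.690/0.716 = 2.95, power 83%.
- ρ = 0.5, 36 visits: variance 18.5/36 = 0.5139, noncentrality 0.5 × 4.690/0.717 = 3.27, power 90%.
- ρ = 0.7: 70% with PIV and 79% without.

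Simulation over three assumed covariances gave 78–80% with PIV and 87–88% without. The loss is about 7 to 10 percentage points.

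**The case against.** Several objections stand and limit the point.

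- **The last visit is undefined.** That it is V-39 at the end of PIV is inferred from the whole-study wording, the MADRS schedule and the visit count. Table 1 labels the phases differently and ticks DTS (V-39 in the text) and SDS (V-35 in the text) at the same phase end, so the visit map is not secure. The fix should name phases rather than visit numbers.
- **The vital-signs contrast is weak evidence of intent.** Vital signs are not scheduled in PIV, so their narrower window follows from the schedule. It is useful only as a model for the wording.
- **The rejection rates rest on assumptions.** No correlation is documented. The runs use complete data, while the withdrawal rules remove non-responders and relapsers, so patients who reach PIV will be a selected group.

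A reader might also infer stronger things that the documents do not support.

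- **PIV compares untreated with treated patients.** This holds only on the Intervention wording, where control tablets continue. The Design wording can be read as all treatment having ended.
- **A sustained benefit is almost invisible to the interaction test.** With 0.5 SD present from the second visit and then constant, interaction power is about 12% under one assumed covariance. If the benefit builds up over the acute month, it is 55% under that covariance and 33–91% under three others.
- **Two primary tests inflate the 5% level.** The article does not name two primary tests. Which ANOVA term decides, and in what order tests are made, is commonly left to an analysis plan that is not shown.
- **A superiority test at the end of PII should be the gatekeeper.** That is one preference among several, and it sits badly with a hypothesis of similar efficacy.

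**Conclusion.** The concern holds in a limited form. The article's own wording puts the post-ketamine month inside the primary MADRS window; this is a stated choice, not an omission. PIV is off ketamine whichever description of it is right.

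Its effect differs by test. The interaction can be significant because of PIV alone: roughly 40% to over 95% of the time for a 0.5 SD difference confined to PIV, against about 5% when PIV is left out. It would be wrong to conclude that the whole ANOVA result can be driven by PIV, because the group effect is only diluted, with power falling from about 87% to about 80% when a 0.5 SD on-drug difference vanishes in PIV. These figures assume 44 per arm, complete data, correlations not found in the documents, and a final visit at the end of PIV. They show a range, not a forecast.

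**What to change.** 1. Limit the primary MADRS model to the acute and maintenance phases (PII and PIII), in the terms already used for vital signs over time, and define the final visit.
2. State in advance which between-arm MADRS contrast within that window is primary, and make it consistent with the similar-efficacy hypothesis. The choice is the sponsor's, provided that one contrast is named.
3. Analyse PIV separately as the course after ketamine.
4. Reconcile Design and study populations with Intervention on what each arm receives in PIV.

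The cost is protocol and analysis-plan wording, with no new data or visits. The downside is that PIV data lose primary status. The article says that the study is under way, so the change should be made and dated before unblinding; a window chosen later would look data-driven.
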